**Fig. 3 Fig3:**
[figure not shown]
Participant timeline: schedule of enrollment, interventions, and assessments

Written informed consent will be obtained from all the participants prior to enrolment by the primary investigator. No invasive procedure(s) will be conducted on the participants. All the information gathered in the course of the study will be kept confidential. Participation or non-participation in the study would not affect the usual treatment of the participants. The participants can withdraw their consent for participation in the study at any point. Participants will be informed that they will undergo either an active or sham training over three days, with assessments before, after, and during follow-ups at 1 and 3 months. Participation is voluntary, with no assured benefits or risks anticipated, and all data will be kept strictly confidential. While the intervention is intended to help, there is a possibility it may not produce the desired therapeutic effect. They will be informed that the sham training is designed to resemble the actual intervention without offering any therapeutic benefit.

During the course of study participation, any increase in distress or complaints noted or reported by the participant will be communicated to the treating team, and necessary referrals will be made. Any such adverse events occurring during the study period will be recorded and reported as per standard reporting guidelines.

#### Sample size {19}

Drawing upon findings from Khan et al. [45], patients exhibited a significant reduction in aggression from a mean of 3.44 (SD = 3.89) to 1.07 (SD = 1.92) on the Overt Aggression Scale—Modified (OAS-M) after the computerized cognitive and social cognition training. The effect size was calculated using the G*Power software (Version 3.1.9.6) with a priori power analysis for a t-test comparing two dependent means (matched pairs) and an assumed correlation of 0.5 between paired measurements [46]. A paired t-test framework was used for effect size estimation because the control group (sham training) in this study serves primarily as a means of studying the mechanism of work of the ICT (i.e., 100% contingency-based associative learning), due to which we employed only 50% contingency between aggressive stimuli and no-go responses in the ST, which as suggested by some of the past literature, opposes how the ICT works [20, 23, 24]. However, recent studies have reported comparable effectiveness of sham and active inhibitory control training, raising uncertainty regarding the specificity of the proposed mechanism [47]. Similar concerns have also been raised in relation to attentional bias modification interventions, which were previously assumed to operate through similar mechanisms but have more recently been shown to give non-specific effects [48]. Therefore, to estimate the expected magnitude of change attributable to inhibitory control training itself, pre–post scores from the experimental condition were used for effect size calculation from prior literature.

According to the above estimates based on the prior literature, with a corresponding effect size of 0.70, power of 80%, and alpha of 0.05, the necessary sample size required to detect a comes out to be at least 26 subjects in each group (i.e., experimental and control) [49].

As per another study conducted at the same tertiary care centre as the current study [50], the dropout rate among patients was about 45% at 1 month, and another 15% increase in dropouts was reported at the 3-month follow-up. Thus, assuming a planned attrition rate of 60% in both groups using this reference, the overall required sample size for the research study is recalculated to 130 participants, with 65 participants in each group.

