### Trial design {12}

The research study will utilize a two-group, parallel, superiority randomized controlled trial (RCT) design. The primary objective of the trial is to determine whether inhibitory control training produces a greater reduction in aggressive behaviour compared to sham training, thereby testing the superiority of the experimental intervention over the comparator. Although the trial is designed as a superiority study, some aspects of it may be exploratory in nature due to our interest in whether the intervention works and how it works. Eligible participants will be randomly allocated in a 1:1 ratio to either the experimental group or the control group. In the experimental group, participants will receive inhibitory control training, while those in the control group will receive a sham version of the training. Both groups will also be receiving treatment as usual (TAU), as decided by the clinical team. Evaluation will occur at four time points: Pre-intervention (baselines), post-intervention at 1-Day post ICT, 1-month post ICT (± 4 Days), and 3-months post ICT (± 7 Days). The trial is designed to evaluate the superiority of Inhibitory Control Training over sham training in reducing aggressive behaviours.

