## Discussion

This study will be the first attempt to examine the efficacy of Inhibitory Control Training (ICT) in reducing aggression among individuals with co-occurring substance use and gambling disorders in the Indian context. Drawing from the Problem Behavior Theory and the Dual Process Model of Addiction, the proposed intervention will target implicit mechanisms of behavior regulation by associating no-go cues with aggression-related stimuli. Unlike conventional therapies focusing on conscious reflection and decision-making, this paradigm makes use of unconscious processing to promote behavioral inhibition. As aggression is frequently observed in individuals with addictive behaviors and is closely linked to control and regulation, the intervention, if proven efficacious, could offer a cost-effective and time-efficient alternative to traditional cognitive-behavioral and anger management interventions. Conversely, should the intervention prove ineffective, the findings would indicate that this may not be a productive area for further exploration. Importantly, the study extends existing literature by contextualizing the intervention in India—a country where research on aggression and gambling in addiction populations remains underrepresented.

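### The sample size enters a one-arm pre-post effect of 0.70 as if it were the ICT-versus-sham difference, so the stated 80% power does not describe the trial's primary comparison

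*Protocol article*

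**What the plan says.** Trial design {12} describes a two-arm, parallel, 1:1 superiority trial whose aim is to "determine whether inhibitory control training produces a greater reduction in aggressive behaviour compared to sham training". Outcomes {16} sets the primary outcome as the change in the OAS-M overall aggression score from baseline to 1 month. Statistical methods {27a} makes training group the between-subjects factor.

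Sample size {19} starts from an earlier study of a different computerised training, in which OAS-M aggression fell "from a mean of 3.44 (SD = 3.89) to 1.07 (SD = 1.92"). It reports using G*Power with an "a priori power analysis for a t-test comparing two dependent means (matched pairs) and an assumed correlation of 0.5 between paired measurements", and says that the paired framework served to estimate the effect size because the sham arm is mainly there to study mechanism. It then states, "with a corresponding effect size of 0.70, power of 80%, and alpha of 0.05", that "the necessary sample size required to detect a comes out to be at least 26 subjects in each group". It neither says whether the test is one- or two-sided nor identifies the test behind the 26. A loss of 60% (45% by 1 month and a further 15% by 3 months) raises 26 to 65 per group, 130 in total.

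The same section concedes that "recent studies have reported comparable effectiveness of sham and active inhibitory control training". The Discussion says that "should the intervention prove ineffective, the findings would indicate that this may not be a productive area for further exploration", and the Abstract carries a similar sentence.

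**The concern.** A pre-post change within one group contains everything that happens to treated patients over time: admission, usual treatment, regression to the mean, repeated assessment and any specific effect of training. The comparison with sham contains only what differs between the arms. Under {12} and Concomitant care {15d}, both arms are inpatients at the start and both receive usual treatment, so some improvement under sham is to be expected. Using the pre-post figure as the between-arm effect assumes zero change under sham, and the section itself cites evidence pointing the other way.

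The derivation also cannot be followed as written, because the only test named does not lead to 26 at the stated inputs.

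Two things are at stake. A reader will take the 80% as the chance of detecting a true ICT benefit over sham, which it is not. And the protocol says in advance what a null result would suggest about the whole approach, although the design may be unable to exclude a moderate benefit.

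**Working it through.** **Inputs, all from Sample size {19} unless noted.** Means 3.44 and 1.07; SDs 3.89 and 1.92; correlation 0.5; effect 0.70; alpha 0.05; power 80%; loss 45% at 1 month and 60% at 3 months; 65 randomised per arm. The primary endpoint at 1 month is from Outcomes {16}. Power is computed with the exact noncentral t distribution. Sidedness is not stated, so both options are shown.

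**1. The effect size reproduces, as a within-group quantity.**
- SD of change = √(3.89² + 1.92² − 2 × 0.5 × 3.89 × 1.92) = 3.37
- dz = (3.44 − 1.07) / 3.37 = 2.37 / 3.37 = 0.70

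**2. Which test gives 26?** Noncentrality is d√n for n pairs and d√(n/2) for n per arm, with d = 0.70 and 80% power.

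| Test at alpha 0.05 | Two-sided | One-sided |
|---|---|---|
| Matched pairs (the test named) | 19 pairs | 15 pairs |
| Independent groups | 34 per arm | **26 per arm** (power 80.1%) |

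With the unrounded effect of 0.703, the paired figures are 18 and 14. With 26 pairs, the two-sided paired test would have 93% power. So the plan's 26 matches a one-sided independent-samples test into which the paired dz was entered as a between-arm d.

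**3. The inflation reproduces.** 26 / (1 − 0.60) = 65 per arm, 130 in total.

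**4. What 130 gives for the between-arm comparison**, two-sided 0.05, unadjusted change score:
- 1 month: 65 × 0.55 = 35.75, about 36 per arm.
- 3 months: 65 × 0.40 = 26 per arm.

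| | 1 month (36 per arm) | 3 months (26 per arm) |
|---|---|---|
| Power if the between-arm d is 0.70 | 83% | 70% |
| Difference detectable with 80% power | 0.67 SD | 0.79 SD |
| Power if the between-arm d is 0.35 | 31% | 24% |

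The 0.35 is an illustration in which sham patients achieve half of the assumed change (0.70 / 2). It is not a figure from the protocol. At a change SD of 3.37, 0.67 SD is 0.67 × 3.37 ≈ 2.3 OAS-M points, nearly the whole 2.37-point change in the source study.

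**5. What a null result could exclude at 1 month.** The 95% confidence interval half-width is about t(0.975, 70) × √(2/36) ≈ 0.47 SD of change. An observed difference of zero would therefore still be compatible with a benefit of nearly half an SD.

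**The case against.** The best defence is that the numbers are not broken. 26, 65 and 130 all follow from a one-sided independent t-test at 0.70. The section describes the paired framework as a way to obtain the effect size and never clearly says that the 26 came from a paired test. The objective is worded directionally. This stands: a reader might infer that the sample size is simply an arithmetic failure, and the documents do not support that. The fault is that the test and its sidedness are undeclared and that the effect entered belongs to a different comparison.

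A reader might also infer from the 70% figure that 130 patients are too few. That does not follow. The 70% belongs to 26 completers per arm at 3 months under a two-sided test, which is a conventional assumption and not something the protocol states. At the 1-month primary endpoint the protocol's own retention gives 83% at 0.70.

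Nor is the 60% loss an error. The primary model in {27a} includes the 3-month visit, so inflating for cumulative loss is conservative and helps the 1-month comparison.

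Finally, the section openly discloses the doubt about sham, and the null-result sentences are hedged. Disclosure does not make the within-group effect valid for sizing a between-arm test, however. And giving sham a mainly mechanistic role does not sit with {12}, where superiority over sham is the primary objective.

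**Conclusion.** The point holds in this form. The justification and the stated power are wrong for the comparison the trial makes; the total of 130 is not shown to be inadequate. The within-group 0.70 applies between arms only under zero change in sham, which the protocol's own evidence calls into question. The named paired test needs 19 pairs (two-sided) or 15 (one-sided), and 26 is recovered only with an undeclared one-sided independent test.

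Under a two-sided 0.05 test of unadjusted change, 130 randomised gives 83% power at 1 month and 70% at 3 months if the between-arm effect really is 0.70, falling to 31% and 24% if it is 0.35. These figures assume the protocol's loss rates, a correlation of 0.5, and a change SD of 3.37 carried over from the source study for the conversion to OAS-M points. How far true power falls below the stated 80% depends on the change under sham, which the documents do not quantify.

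**What to change.** Keep 130 and rewrite the justification in Sample size {19}:

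- Delete the paired-test derivation. Name the test and state its sidedness.
- If the test is a two-sided independent comparison of change to 1 month, state: 65 per arm, 45% loss, about 36 per arm, 80% power for a between-arm difference of about 0.67 SD of change (about 2.3 OAS-M points at a change SD of 3.37).
- For 3 months with 26 per arm, state a detectable difference of about 0.79 SD, or 70% power at 0.70.
- Say that power is lower if sham is active, for example 31% at 1 month and 24% at 3 months for a difference of 0.35 SD on the unadjusted change score.
- Do not claim a smaller detectable difference from baseline adjustment by scaling 0.67 × √(1 − 0.5²) = 0.58. That assumes equal SDs before and after, whereas the source SDs are 3.89 and 1.92.

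In the Abstract and the Discussion, make the null-result sentences conditional: conclude lack of worthwhile benefit only if the 95% confidence interval excludes a smallest worthwhile difference fixed in advance.

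The cost is a rewritten section and two sentences, with no extra patients. Under Interim analyses {28b}, all analysis follows completion of data collection, so the change can be made before any analysis. The downside is that the stated power becomes less favourable.

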#### Recruitment {20}

Regular screening for inclusion and exclusion criteria will be conducted in the inpatient department of the recruitment site several times per week to identify newly admitted patients who meet the eligibility requirements.

## Assignment of interventions: randomisation

### Sequence generation: who will generate the sequence {21a}

The random allocation sequence will be generated by an independent biostatistician who is not involved in participant recruitment, intervention delivery, or outcome assessment. The allocation sequence will be generated using the R software [51].

### Sequence generation: type of randomisation {21b}

Restricted randomisation using permuted block randomisation will be employed to ensure balanced allocation between the experimental and control groups. Randomized block sizes of 4, 6, and 8 will be used to reduce predictability of the allocation sequence. No stratification factors will be applied.

### Allocation concealment mechanism {22}

Allocation concealment will be ensured using the Sequentially Numbered, Opaque, Sealed Envelopes (SNOSE) [52] method. The random allocation sequence will be placed into sealed envelopes by a researcher not involved in participant enrolment or intervention delivery. Envelopes will be opened sequentially only after a participant has provided written informed consent.

### Implementation {23}

The primary investigator responsible for participant enrolment, intervention delivery, and outcome assessment will not have access to the random allocation sequence prior to participant assignment. Group allocation will be revealed to the primary investigator only at the time of opening the sealed envelope.

## Assignment of interventions: blinding

### Who will be blinded {24a}

Only trial participants will remain blinded to allocation throughout the study period, making it a single-blind study. Investigator blinding was not feasible, as all aspects of participant enrolment, intervention delivery, outcome assessment, and analysis are conducted by a single investigator.

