### Explanation for the choice of comparator {9b}

ST will be matched with active training in terms of both stimulus exposure and response requirements, but will have the contingency agreement reduced to 50%, thereby preventing the formation of associations between aggressive stimuli and inhibitory responses. Similar studies in the past have used sham training as a comparator where stimuli were presented in a way that prevents any form of association [20, 23, 24]. Some other studies working with a different population have also shown the same [25]. Another reason for the inclusion of sham training in the control group is that while controlling for time and attention, it might provide information into the underlying mechanism of functioning of this intervention—differential effects between the groups, if observed, can be attributed to the formation of implicit inhibitory associations.

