#### Participant timeline {18}

Patients admitted to the National Drug Dependence Treatment Centre (NDDTC) will be administered upon a brief screening process. The screening will initiate only when the participant is able to actively engage in the study, ensuring they are not intoxicated or in a state of withdrawal. Withdrawal charting will be done using the Clinical Institute Withdrawal Assessment of Alcohol Scale, Revised (CIWA – Ar) [40] for alcohol, Clinical Opiate Withdrawal Scale (COWS) [41] for opioids, Minnesota Nicotine Withdrawal Scale (MNWS) [42], the Cannabis Withdrawal Scale (CWS) [43] for cannabis, and the Clinical Institute Withdrawal Assessment Benzodiazepines (CIWA—B) [44] scale for Benzodiazepines. If the participant is found intoxicated or experiencing withdrawal, the screening process will be paused. It will be resumed only after a reassessment of withdrawal symptoms has been conducted within the next 24–48 h.

Patients diagnosed with substance use disorder by a psychiatrist will then undergo the South Oaks Gambling Screen (SOGS) for the identification of problem or pathological gambling in the patients. Once it is ascertained that the participant fulfills the inclusion/exclusion criteria, written consent will be taken by the primary investigator, and patients will be randomized to either the experimental or control group. The Alcohol, Smoking, and Substance Involvement Screening Test (WHO-ASSIST Version 3.0) and the Overt Aggression Scale – Modified (OAS – M) will be administered along with the sociodemographic and clinical proformas. Other baseline assessments, including the Stimulus Evaluation Task, Inhibitory Control Task, and the Timeline Follow-Back Scale (TLFB) will also be performed post randomization. All questionnaires and assessments will be administered by verbally posing the questions (and options) to the patients. The demographic details, medical/psychiatric history of the participant, their family history, and treatment record will also be recorded (see Supplementary File 2).

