## Data management {26}

Data from our electronic word files will be copied and stored in Microsoft® Excel for Mac (Version 16.104) by the primary investigator. Periodic checks will be conducted for completeness and consistency. Range checks will also be implemented following data entry to ensure that the data values are appropriate. Final datasets will be secured and retained in accordance with institutional data management policies. All trial datasets will remain shared with the supervisor of the doctoral study (Corresponding Author).

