### How missing data will be handled in the analysis {27c}

The method of data imputation will be chosen based on the characteristics and nature of the missing data following completion of data collection, ensuring appropriate handling of any incomplete data points.

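### One investigator who knows the allocation trains, rates the primary outcome and analyses, yet the protocol attributes any group difference to the mechanism and does not list unblinded rating as a limitation

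*Protocol article*

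**What the plan says.** **Who knows the allocation.** Under Who will be blinded {24a}: "Only trial participants will remain blinded to allocation throughout the study period, making it a single-blind study". The reason given is "Investigator blinding was not feasible, as all aspects of participant enrolment, intervention delivery, outcome assessment, and analysis are conducted by a single investigator". Under Implementation {23}: "Group allocation will be revealed to the primary investigator only at the time of opening the sealed envelope". From then on the investigator knows the arm, and the unblinding section {24c} confirms access to the allocation of every enrolled participant.

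**What that person does.** The adherence section {15c} has the primary investigator deliver all six sessions in person. The outcome collection section {25a} has the same person conduct all assessments by interview. Participant timeline {18} places the OAS-M after the randomisation step and says that other baseline measures "will also be performed post randomization".

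**The primary outcome.** Outcomes {16} defines it as the change in overall OAS-M aggression score from baseline to 1 month. The OAS-M is a semi-structured interview. Each subscore is the number of behaviours in the past week multiplied by a severity level.

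**The analysis.** The statistical methods {27a} leave the choice between parametric and non-parametric tests until the collected data have been checked against assumptions. On missing data {27c}: "The method of data imputation will be chosen based on the characteristics and nature of the missing data following completion of data collection". The protocol says that its analysis plan is contained in this document {5}.

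**The conclusion to be drawn.** The comparator section {9b} says that "differential effects between the groups, if observed, can be attributed to the formation of implicit inhibitory associations". Expected limitations and strengths names the male inpatient sample, the short training, an inconclusive mechanism and the artificial task, but not unblinded rating or analysis.

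**Others attached to the trial.** The sequence is "generated by an independent biostatistician who is not involved in participant recruitment, intervention delivery, or outcome assessment" {21a}. A seven-member Doctoral Committee covers psychiatry, clinical psychology and/or biostatistics {3d}.

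**The concern.** The primary score depends on judgement at three steps: how the interview is conducted, which events are counted, and what severity each is given. Because count and severity are multiplied, a lenient or strict judgement on one is scaled by the other. The person making these judgements has delivered the training and knows which version each participant received. The baseline rating may be exposed too, since it appears to follow allocation.

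The same person then conducts the analysis, with test and imputation still open. Loss to follow-up is expected to be heavy (45% by 1 month), so the imputation choice could matter a great deal.

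If ICT comes out better, three explanations compete: the trained association, the rater's expectation, and choices made in the analysis. The comparator section allows only the first. A reader who looks to the limitations for the second and third will not find them.

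**Working it through.** **1. Is the obstacle to blinding inherent?** The stated reason is that one person does everything. That is a matter of staffing and not a property of the training. It has to be tested separately for each role.

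- *Delivery:* the trainer must know the arm.
- *Rating:* a masked rater would be a further person. The documents name nobody shown to be masked, trained in the OAS-M and available.
- *Analysis:* the protocol already has an independent biostatistician and a committee whose stated expertise includes biostatistics. No interim analysis is planned {28b}, and analysis follows the end of enrolment, expected in December 2026 (Trial status). Masked analysis can therefore still be arranged.

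**2. Do the participant-side safeguards cover the problem?** Participants are masked, are not told that aggression is the target, and are asked at the end to guess their group {24b}. These measures address participants' expectations, not the rater's or the analyst's.

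**3. How much could rating bias matter?** The protocol has no figure for this, so the bias is an assumption and is shown as a range.

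Inputs:
- 65 per arm (Sample size {19}). This reproduces from the protocol's own 26 per group and 60% attrition: 26 / (1 − 0.60) = 65.
- 1-month dropout 45% (same section): 65 × 0.55 = 35.75, taken as n = 36 per arm.
- Two-sided test at 0.05. The section gives alpha 0.05 without sidedness, so two-sided is assumed.
- True effect zero. Rating shift b, in SD units, in favour of ICT (assumed).

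Formula for a two-sample t-test: df = 2n − 2 = 70, critical value 1.994, noncentrality = b × √(n/2) = b × √18 = 4.243b. The chance of a significant result favouring ICT is the probability that a noncentral t exceeds 1.994.

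| b (SD) | Noncentrality | 36 per arm | 26 per arm | 65 per arm |
|---|---|---|---|---|
| 0 | 0 | 2.5% | 2.5% | 2.5% |
| 0.10 | 0.42 | 6.2% | 5.4% | 8.2% |
| 0.20 | 0.85 | 13.1% | 10.5% | 20.4% |
| 0.30 | 1.27 | 24.1% | 18.4% | 39.7% |

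The noncentrality column is for 36 per arm. The last two columns bracket the result, from the pre-attrition requirement to complete follow-up.

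**4. What is such a shift in OAS-M points?** The outcome is a change, so the SD of change is the relevant unit. From the figures in Sample size {19} (SDs 3.89 and 1.92, assumed correlation 0.5): √(3.89² + 1.92² − 2 × 0.5 × 3.89 × 1.92) = √11.35 = 3.37. A shift of 0.10 SD is 0.34 points and 0.30 SD is 1.01 points. The mean fall in the source study was 3.44 − 1.07 = 2.37 points.

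**5. What would masked analysis change?** It removes the freedom to choose methods with arm in view. It does nothing to the shift in steps 3 and 4, which is already in the recorded scores. The sample size stays at 130.

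**The case against.** The single-blind design is disclosed with its reason, and a doctoral project run by one person has limits. Participant masking is thorough for a trial of this kind. The protocol is also not uniformly confident about mechanism. The sentence in {9b} opens by saying only that sham training might be informative, Sample size {19} cites evidence that casts doubt on specificity, and the limitations call the mechanism inconclusive. All of this stands, and it tempers the criticism of the attribution. It does not supply the missing caveat, because doubt about mechanism is a different matter from a rater who knows the arm.

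Four stronger readings go beyond the documents.

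- *That the protocol has the investigator pick tests and imputation from arm-labelled data.* The analysis sections name no decider and mention no arm labels. They tie the choices to assumptions and to the nature of the missing data. The committee section {3d} requires all seven members to consent to relevant trial decisions. What can be said is that the person conducting the analysis knows the allocation, the choices come late, and no masking is described.
- *That severity could be scored masked by people already on the trial.* The protocol says "All trial datasets will remain shared with the supervisor of the doctoral study", but not that the supervisor is unaware of allocation, trained on the OAS-M or available. The incidents would still be elicited and written down by the unblinded interviewer. Enrolment began in January 2025, so a change of rater could leave two scoring regimes.
- *That coded arm labels would be enough.* They cannot mask an investigator who opened each envelope, or a biostatistician who holds the key.
- *That bias must favour ICT.* That direction is plausible, but the documents do not establish it.

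**Conclusion.** The point holds for what can be concluded and for the analysis. An unblinded trainer-rater, a judgement-based primary outcome and late analysis choices mean that a difference favouring ICT could not be attributed to implicit associations alone. The protocol should not say that it can.

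The size is illustrative. With 36 per arm and no true effect, assumed shifts of 0.10 to 0.30 SD move the chance of a significant result favouring ICT from 2.5% to between about 6% and 24%. This rests on the 45% dropout figure, a two-sided two-sample t-test on completers and a bias size that the documents do not give. It describes the rating component only. A reader might take it as the gain from masking the analysis, which it is not. The effect of late analysis choices has not been quantified.

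**What to change.** 1. **Fix the analysis without arm.** Before any arm-labelled analysis, settle the primary model, any transformation or choice of test, and the imputation method on pooled data with the arm variable removed. Have the Doctoral Committee record its agreement with a date. The imputation method will then be chosen without sight of dropout by arm, so state at that point how recoded arm enters the imputation model.
2. **Have someone else run the primary analysis on recoded arms.** This should be a person with biostatistics expertise already attached to the trial, for example on the Doctoral Committee, who does not hold the key. The biostatistician who generated the sequence keeps the key and so does not run the analysis. Recode the arms and leave training-session fields out of the file, because the two schedules differ (Tables 1 and 2) and would reveal the arm.
3. **Correct the claims.** In the comparator section {9b}, say that a group difference would be consistent with the proposed mechanism but could also reflect unblinded rating. In Expected limitations and strengths, list unblinded outcome assessment.

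**Cost:** a few hours of statistician time and a short amendment, which goes to the ethics committee under Protocol amendments {31}. The sample size does not change. The committee's expertise is described with and/or, so confirm that a member can take on the analysis. Bias from the unblinded interview remains, which is why the third change is needed alongside the first two.
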